## 4. Secondary Research Objective

The secondary objectives of this study are to assess the efficacy of brain modulation via 20 Hz rTMS targeting the right dorsolateral prefrontal cortex, in conjunction with simultaneous traumatic memory reactivation, on the following aspects:Different dimensions of PTSD assessed using CAPS-5 at M3 and M6 post-treatment;The severity of PTSD assessed using PCL at each visit;Anxiety symptoms at V13 (end of treatment), M1, M3, and M6 post-treatment;Depressive symptoms at V13 (end of treatment), M1, M3, and M6 post-treatment;Changes in social cognition at M3 post-treatment;Changes in quality of life at M1, M3, and M6 post-treatment;The safety of the intervention.

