### 5.4. Intervention

#### 5.4.1. rTMS Protocol

The intervention consists of 12 HF-rTMS sessions in the right DLPFC (rDLPFC) on 12 workdays. The HF-rTMS parameters of the active intervention are as follows: active high-frequency 20 Hz, 3 to 4 sessions of 10 min per week, 2000 pulses/session, and a motor threshold of 110%. In our centers, we regularly offer 3 to 4 rTMS sessions per week for patients with depression, which has proven to be both feasible in terms of logistics and well accepted by the patients receiving the treatment. The number of sessions per week will be determined based on the logistical constraints of the investigating centers and the patients being stimulated. The device used will be an electromagnetic stimulator, which is used to artificially provoke a functional activity (GMDN 13762) CE marked, Class IIa.

The rDLPFC will be located at position F4 using the International 10–20 EEG system or a neuronavigation system. During the stimulation, participants will be seated on a comfortable chair with extra neck support. One stimulation session will take approximately 10 min.

The motor threshold will be determined at rest before the first stimulation session, using single-pulse TMS in combination with motor-evoked potentials. The optimal spot on the scalp for stimulation of the right abductor pollicis brevis muscle will be located, and the motor threshold will be established by delivering single stimulations to the motor cortex. The motor threshold, defined as the lowest stimulation intensity producing five motor evoked potentials (MEPs) of at least 50 μV in 5 out of 10 stimulations, will be measured by gradually increasing the stimulation intensity. The intervention will be applied by an rTMS-trained researcher.

Sham rTMS will be delivered, following the same procedure. The trauma memory reactivation procedure will be the same as that in the experimental group. Sham rTMS will be performed with a special probe for sham procedures. The instruction to use sham rTMS will be the same as that for the active device. A sham coil providing the same noise, heat, clicks, and sensations as the active coil will be used without any magnetic pulse.

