### 7.3. Secondary Outcome Measures

PTSD severity scores at M3 and M6 (repetition, avoidance, and neurovegetative activation) measured using CAPS-5 (structured interview);PTSD severity score measured using the PTSD Checklist (PCL-5 self-questionnaire) at M1, M3, and M6;Dissociative symptom severity scores assessed by the Clinician-Administered Dissociative States Scale (CADSS), the Multidimensional Assessment of Interoceptive Awareness (MAIA), and the Dissociative Experiences Scale (DES) at V1, V13, M1, M3, and M6.The severity scores of the dimensions of anxiety (measured using HAM-A) and depression (measured using HAM-D) at M1, M3, and M6.Social cognition at M0 and M3 assessed using the Eckman test, “reading the Mind in the Eyes” test (Baron-Cohen, test des Faux-Pas (Baron-Cohen), Empathy Quotient questionnaire (Baron-Cohen), and Toronto Alexithymia Scale (TAS-20).Quality of life assessed using WHOQOL EuroQol Health Measure, EQ-5D-5L;Proportion of adverse events during the active treatment phase and during the follow-up.

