## 8. Statistical Analyses

### 8.1. Power Analysis

The current study is the first to investigate the effect of multiple reactivation therapies enhanced by 20 Hz HF-rTMS sessions on PTSD score severity six months after the last stimulation session. To the best of our knowledge, no studies have investigated the effect of rTMS on PTSD after such a period. A detailed analysis plan will be defined before the database lock. The analysis will be performed by a statistician from URC-Est after data review and database lock. Therefore, no interim analysis is planned. Analyses will be performed using SAS^®^ software (version 9.4 or the updated version).

Based on the literature, we estimate that the CAPS total severity score at M1 in the sham rTMS + memory reactivation procedure group will be at 50 ± 24 (S5 value from [15]). Assuming a 15-point reduction in the experimental group to indicate a clinically significant difference based on the CAPS manual, two-sided alpha = 5% and beta = 15%, and a standard error of 24 in both groups, 92 patients are needed (Student *t*-test, East 6, Cytel). Considering 10% of non-evaluable patients, 102 randomized patients are needed. We anticipate fewer non-evaluable patients than in Kozel’s study (4). Our reactivation memory is less demanding for patients than that of Kozel’s program. Regarding the CAPS score at inclusion, we anticipate a comparable score for the overall severity. This score is close to that reported in Yan’s meta-analysis (3) on the efficiency of rTMS in PTSD. There is empirical evidence regarding the value of prolonged exposure to a wide range of injuries. However, clinical trials have shown that less than 50% of patients improve with exposure therapy and only 15% achieve complete remission [16]. In our study, we will include a more resistant population that is classically less sensitive to the effects of psychotherapy alone. All tests will be two-sided, and a *p*-value of <0.05 will be considered significant.

The baseline characteristics of the patients will be described overall and for each group. Qualitative data will be described with frequencies and percentages and quantitative data will be described with mean and standard error or with median and interquartile interval according to the distribution of the variable.

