### 8.3. Secondary Criteria Analysis

PTSD severity scores at V15 and V16 (repetition, avoidance, and neurovegetative activation) measured with CAPS (structured interview) will be described by mean and standard deviation, and the mean difference between groups will be calculated using its 95% confidence interval (CI). Each score (PCLS self-questionnaire, HAM-A, and HAM-D scores) will be analyzed in the same way at V14, V15, and V16. Graphical representations of the evolution over time will be performed. The mean difference between groups and 95% CI will be calculated.

Based on the PTSD severity score measured using the PTSD Checklist (PCLS self-questionnaire), a linear mixed regression model may be performed with the patient as a random effect and the group as a fixed effect. In the case of a non-normal distribution of the interest variable, a transformation will be performed.

Social cognition at V0 and 15 will be assessed by the Eckman test, “Reading the Mind in the Eyes” test [17], Test of Faux-Pas [18], Empathy Quotient questionnaire [19], and Toronto Alexithymia Scale (TAS-20) [20]. The demonstration of cognitive improvement requires a free interval between the end of the active treatment phase and the completion of the assessment. The difference between the M3 and V0 measurements of each test will be calculated using their 95% CI. The evolution of quality of life (assessed using the WHOQOL [21] and EuroQol Health Measure, EQ-5D-5L [22]) will be analyzed. Each subscore of the two scales will be described and analyzed in the same way.

The proportion of at least one adverse event observed during the active treatment phase and during the follow-up will be described and compared between groups using Fisher’s exact test. The proportion difference between groups and their 95% CI will also be calculated. Each type of adverse event will also be described by the group.

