## Figures and Tables

**Figure 1 brainsci-13-01274-f001:**
[figure not shown]
Overview of the intervention.

**Table 1 brainsci-13-01274-t001:** Overview of instruments and assessment.

Visit	0	1	2	3	4	5	6	7	8	9	10	11	12	13	14	**15**	**16**
PDI	✕																
HCG		✕															
Active/Sham rTMS			✕	✕	✕	✕	✕	✕	✕	✕	✕	✕	✕	✕			
Trauma Script		✕															
Reactivation			✕	✕	✕	✕	✕	✕	✕	✕	✕	✕	✕	✕			
MINI-5		✕													✕		
CAPS-5	✕														✕	✕	✕
PCL-5	✕		✕			✕			✕			✕		✕	✕	✕	✕
CGI			✕			✕			✕			✕		✕	✕	✕	✕
Eckman Test		✕														✕	
Empathy Quotient		✕														✕	
Baron-Cohen		✕														✕	
TAS-20		✕														✕	
HAM-D		✕												✕	✕	✕	✕
HAM-A		✕												✕	✕	✕	✕
WHOQOL		✕													✕	✕	✕
EQ-5D-5L		✕													✕	✕	✕

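### The optional PCL mixed model names group as its only fixed effect and does not say which visits enter, so it yields one average arm difference, ignores baseline PCL-5, and is diluted if pre-treatment and on-treatment visits are used

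*Protocol article*

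**What the plan says.** All references are to the protocol article.

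- **Model (section 8.3).** For the PTSD Checklist, "a linear mixed regression model may be performed with the patient as a random effect and the group as a fixed effect". The wording is permissive. No term for visit, group-by-visit or baseline is named, and the visits to be entered are not stated.
- **Objective (section 4).** "The severity of PTSD assessed using PCL at each visit".
- **Outcome definition (section 7.3).** "PTSD severity score measured using the PTSD Checklist (PCL-5 self-questionnaire) at M1, M3, and M6".
- **Schedule (Table 1, "Overview of instruments and assessment").** PCL-5 is marked at nine of the 17 visits: V0, V2, V5, V8, V11, V13, V14, V15 and V16. Stimulation is marked from V2 to V13, which matches section 5.4.1: "The intervention consists of 12 HF-rTMS sessions in the right DLPFC (rDLPFC) on 12 workdays". V0 is therefore before treatment, and V2 is the day of the first session.
- **By-visit analysis (section 8.3, before the model).** "Each score (PCLS self-questionnaire, HAM-A, and HAM-D scores) will be analyzed in the same way at V14, V15, and V16", that is, by mean differences with 95% CI. Graphs of the course over time are also planned.

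Section 8.3 and Table 1 together imply V14 = M1, V15 = M3 and V16 = M6. Section 8.3 calls the scale PCLS where section 7.3 and Table 1 call it PCL-5. I take these to be the same instrument.

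**The concern.** A model with a random patient effect and group as the only fixed effect assumes one constant arm difference over every visit entered. Randomisation makes the expected difference at V0 zero. During the course of sessions the difference may still be growing. If those visits are outcomes, the coefficient averages null, partial and full effects, and it would understate the effect after treatment if read as such.

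If only the three follow-up visits enter, that dilution disappears for a sustained effect. Two limits remain: the model cannot distinguish a lasting effect from a fading one, and it makes no use of the PCL-5 collected at V0. On either reading it does not deliver a result by visit.

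**Working it through.** **Reference figure.** The plan gives no sample size or power for PCL. Its CAPS calculation supplies the group size used below. From "Assuming a 15-point reduction in the experimental group to indicate a clinically significant difference" and "a standard error of 24 in both groups, 92 patients are needed" (the 24 must be a standard deviation), with two-sided 5% and 85% power:

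n per arm = 2 × (1.960 + 1.036)² × (24/15)² = 46, so 92 in total. The plan's 92 reproduces.

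**Step 1: what the coefficient estimates.** In balanced data, the group coefficient of a random-intercept model with group only is the unweighted mean of the visit-specific arm differences.

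**Step 2: share of the full effect recovered.** The time course is an assumption. For a linear build-up over 12 sessions, the sessions received by V0, V2, V5, V8, V11, V13, V14, V15 and V16 are:

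- rated after the day's session: 0, 1, 4, 7, 10, 12, 12, 12, 12 (sum 70); 70/(9 × 12) = 0.648
- rated before it: 0, 0, 3, 6, 9, 11, 12, 12, 12 (sum 65); 65/(9 × 12) = 0.602

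| Assumed time course | All nine visits | Without V0 | M1, M3, M6 only |
|---|---|---|---|
| Full effect at every visit after V2 | 7/9 = 78% | 7/8 = 88% | 100% |
| Linear, rated after session | 65% | 70/96 = 73% | 100% |
| Linear, rated before session | 60% | 65/96 = 68% | 100% |
| Full effect only from V13 | 4/9 = 44% | 4/8 = 50% | 100% |
| Full effect only from V14 | 3/9 = 33% | 3/8 = 38% | 100% |

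These shares do not depend on the effect size or the SD.

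**Step 3: simulation check.** Settings: 150 runs, 46 per arm, true full effect −15, SD 24, correlation 0.6, linear build-up rated before sessions. The group-only model on nine visits averaged −8.5 (expected 0.602 × −15 = −9.0). On M1, M3 and M6 it averaged −14.4. With visit and group-by-visit terms, the M1 contrast averaged −14.7.

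**Step 4: power.** Assume a full effect of 0.5 SD, 46 per arm and equal correlation ρ between visits. In SD² units, the variance of a patient's mean over k visits is v = (1 + (k − 1)ρ)/k. Adjusting the three-visit mean for V0 gives v = (1 + 2ρ)/3 − ρ². Power = Φ(effect/√(2v/46) − 1.96).

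At ρ = 0.6:
- nine visits, rated before: v = 0.644, effect 0.5 × 0.602 = 0.301, SE 0.167, power Φ(1.80 − 1.96) = 44%
- V14-V16, group only: v = 0.733, SE 0.179, power Φ(2.80 − 1.96) = 80% (79% with the t distribution)
- V14-V16, adjusted for V0: v = 0.373, SE 0.127, power Φ(3.92 − 1.96) = 98% (97% with the t distribution)

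| ρ | Nine visits, group only (rated before / after) | V14-V16, group only | V14-V16, V0 as covariate |
|---|---|---|---|
| 0.4 | 56% / 62% | 87% | 95% |
| 0.6 | 44% / 49% | 80% | 98% |
| 0.8 | 36% / 40% | 73% | over 99% |

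One unadjusted visit has 67% power. With the CAPS ratio 15/24 = 0.625 as the effect and linear build-up rated before sessions, power at ρ = 0.4, 0.6 and 0.8 is 75%, 61% and 51% for nine visits, and 97%, 94% and 90% for V14-V16. The gain in the last column of the table comes from baseline adjustment, not from the visit terms.

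**Step 5: change over time.** Effects of 1, 0.5 and 0 of the full effect at M1, M3 and M6 average (1 + 0.5 + 0)/3 = 0.5. A constant effect of 0.5 gives the same coefficient.

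**The case against.** The strongest reply is that the dilution is not in the text. Section 8.3 does not say which visits enter. Section 7.3 limits the PCL outcome to three post-treatment visits, and the preceding sentences of section 8.3 analyse PCL at those same visits. Table 1 says when data are collected, not which data a model uses. On this narrow reading a sustained effect is fully recovered, and the group-only model has more power than a single unadjusted visit (80% against 67% at ρ = 0.6). **This stands**, so the dilution is conditional. The wording in section 4, and the choice of PCL for a mixed model when it is measured repeatedly during treatment, make the wider reading plausible but do not establish it.

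It is also fair that separate PCL differences at V14, V15 and V16 are planned. Whether the effect fades between M1 and M6 will therefore be visible outside the model. Only the on-treatment visits lack a stated by-visit analysis.

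One could add that omitting visit leaves the shared improvement in the residual. In balanced data this does not harm the arm test: the coefficient and its standard error are the same with and without a visit term. Unequal dropout could change that, but the conclusion here does not rest on it.

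Finally, the model is optional and secondary, an article condenses, and a detailed analysis plan is to follow. That explains silence on covariance structure or site. It does not cover a model whose random and fixed effects are both named, nor three places in one article that disagree on PCL timing.

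**Conclusion.** The point holds in a limited form. As written, the PCL model gives one average arm difference, cannot meet the by-visit objective in section 4, and leaves V0 PCL-5 unused. Sections 4 and 7.3 and Table 1 do not agree on when PCL counts as an outcome, and section 8.3 does not settle which visits the model uses.

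- **If all nine visits enter as outcomes:** the coefficient is about 60-65% of the post-treatment effect under linear build-up, and 33-78% across the other time courses tried.
- **If only M1, M3 and M6 enter:** a sustained effect is not diluted. What is lost is baseline precision (about 79% against 97% power at 0.5 SD and ρ = 0.6) and any view, within the model, of a change over time.

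A reader might infer that the plan commits to averaging in pre-treatment visits and so will report an effect 35-40% too small. The documents do not support that, because no text enters those visits in the model.

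The time course, the correlation, the 0.5 SD effect and complete data are my assumptions. The primary CAPS comparison and the planned V14-V16 PCL differences are untouched, so this is a worthwhile correction and not a threat to the trial's main conclusion.

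**What to change.** 1. Reconcile the PCL visits across sections 4, 7.3 and 8.3 and Table 1, and state which post-baseline visits enter the model. Say also whether the V2 rating precedes the first stimulation. If it does, V2 is a second pre-treatment measure and not an outcome.
2. Specify arm, visit (categorical) and arm-by-visit as fixed effects, V0 PCL-5 as a covariate and not an outcome, and a within-patient correlation (a random intercept is enough).
3. Report the arm contrast with its 95% CI at each post-treatment visit.

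A site term, an unstructured covariance and a firm commitment to run the model are optional extras that this point does not need.

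The cost is a few sentences in the detailed analysis plan, which section 8.1 says is still to be defined before database lock, and a few lines of SAS. No new data are needed, since PCL-5 at V0 is already scheduled.

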Furthermore, two trials [12,15] combined rTMS with trauma-focused psychotherapy (the subject recalls their traumatic event) to determine if the combination has an additive effect. Only Isserles et al. (included in the meta-analysis) used recall cues concurrently with stimulation. The primary outcome measure was the CAPS, measured after four treatment weeks. Mean CAPS scores improved from 88 (±5.5) at baseline to 61 (±8.8) in the EXP-STIM group (N = 9), from 86 (±5.4) to 76 (±10.9) in the NOEXP-STIM group (N = 8), and from 86 (±9.2) to 76 (±10.7) in the EXP-SHAM group (N = 9). Significant improvement was demonstrated in the intrusive component of the CAPS scale in patients administered rTMS after exposure to the traumatic event script. The limited number of subjects encouraged the execution of a larger study on a more homogeneous population (resistant PTSD, for example). The study by Kozel et al. is the largest study to date, with 103 veterans randomized to either 9 active (*n* = 54) or sham (*n* = 49) low-frequency (LF) rTMS sessions (1/week) associated with CPT [15]. The rTMS combined with the CPT group showed greater symptom reductions from baseline on CAPS-5 across CPT sessions (t(df ≥ 327) ≤ −2.01 *p* = 0.023, one-tailed). It was a predominantly military population with different traumas from civilian injuries (sexual assault or serious accidents). LF rTMS sessions were performed before psychotherapy.

The rTMS has shown promise as a potential treatment for PTSD, with some studies suggesting that high-frequency stimulation may improve symptoms by modulating prefrontal cortex activity. However, further research is needed to determine the optimal stimulation parameters and patient populations for this intervention. Additionally, more extensive trials exploring the combination of rTMS with trauma-focused psychotherapy may help elucidate whether these treatments have additive effects on PTSD symptom improvement. Considering Yan’s meta-analysis and Kozel’s results, the heterogeneity in rTMS protocols and the limited number of rTMS studies combining cue exposure make it difficult to draw conclusions about the role of rTMS in PTSD. There is a need for intensive clinical trials in this area. We hypothesize greater efficacy of high-frequency (HF) rTMS compared to low-frequency (LF) rTMS [9], as well as improved synergistic action when rTMS and exposure therapy are performed simultaneously, potentially inhibiting the hyperactive amygdala.

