The present study protocol aims to elucidate the effect of multiple sessions of HF-rTMS on PTSD symptoms, cognition, and brain functioning. We will conduct a multicenter, double-blind, randomized controlled trial with 102 PTSD patients randomized (1:1) to either 10 sessions of active HF-rTMS + reactivation therapy or 10 sessions of sham HF-rTMS + reactivation therapy. We will investigate the effect of active versus sham HF-rTMS treatment on measures of symptoms and cognition. We expect reduced symptomatology and improved functioning of neurocognitive tasks in the active HF-rTMS-treated group compared to the sham HF-rTMS-treated group. Our protocol proposes a larger number of pulses than the existing literature. We will evaluate the efficacy of combining neuromodulation through rTMS with script-driven imagery in civilian patients who respond insufficiently to first-line treatments with antidepressants.

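### The only analysis stated for the social cognition tests is a pre-post change, which does not match the active-versus-sham aim, and its baseline visit conflicts with Table 1

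*Protocol article*

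**What the plan says.** In the protocol article, section 8.3 (Secondary Criteria Analysis) names the visits for the social cognition battery, "Social cognition at V0 and 15 will be assessed by the Eckman test" and the other tests, and then gives the single estimate: "The difference between the M3 and V0 measurements of each test will be calculated using their 95% CI". The battery has five tests: Eckman, Reading the Mind in the Eyes, Faux-Pas, Empathy Quotient and TAS-20. No comparison between arms is named for them.

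The aim is set out in the Background: "We will investigate the effect of active versus sham HF-rTMS treatment on measures of symptoms and cognition". The expected result is also comparative: "improved functioning of neurocognitive tasks in the active HF-rTMS-treated group compared to the sham HF-rTMS-treated group". Section 4 lists the objective as "Changes in social cognition at M3 post-treatment", among aspects on which the efficacy of rTMS is to be assessed.

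On the baseline visit, section 7.3 says "Social cognition at M0 and M3 assessed using the Eckman test", while Table 1 ("Overview of instruments and assessment") marks the social cognition rows at visits 1 and 15 and leaves visit 0 blank.

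**The concern.** The estimate that is written down does not answer the question that is asked. Under section 5.4.1 the sham arm goes through the same trauma reactivation as the active arm, and all patients repeat the same tests. An M3-minus-baseline change in either arm, or in both pooled, therefore contains any effect of reactivation therapy, practice on the tests and the passage of time, as well as any effect of rTMS. Only the contrast between randomised arms removes the shared part.

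The wording is more than a shortened form of the same analysis. Within section 8.3 the group contrast is spelled out for the symptom scores, and adverse events get a between-group test. For social cognition a different quantity is named, and the M3 timing is justified by what is needed to demonstrate cognitive improvement. An analysis plan that copied this wording would report intervals for change that do not bear on the randomised question. The abstract names neurocognitive functioning next to PTSD symptoms as something the trial assesses.

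Separately, the change is taken from a visit at which the schedule shows no social cognition measurement.

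**Working it through.** **1. Stated analyses in section 8.3, side by side**

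| Outcome | Quantity stated | Group contrast named? |
|---|---|---|
| CAPS dimensions at V15, V16 | Mean difference between groups, 95% CI | Yes |
| PCL, HAM-A, HAM-D at V14, V15, V16 | Same as CAPS | Yes |
| Social cognition (five tests) | M3 minus V0, 95% CI | No |
| WHOQOL, EQ-5D-5L | Change over time; method given by back-reference | Unclear |
| Adverse events | Fisher's exact test and difference in proportions | Yes |

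**2. Baseline visit for social cognition**

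| Place | Baseline | Follow-up |
|---|---|---|
| Section 7.3 | M0 | M3 |
| Section 8.3 | V0 | V15 (M3) |
| Table 1 (Eckman, Empathy Quotient, Baron-Cohen, TAS-20 rows) | Visit 1 | Visit 15 |

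In Table 1 the first rTMS session is visit 2. Visits 0 and 1 both precede treatment, so a pre-treatment value exists whichever label is right.

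**3. Number per arm for the illustration**

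The article gives no figure for social cognition, so the per-arm number comes from section 8.1: difference 15, SD 24 (printed there as a standard error), two-sided alpha 5%, power 85%.

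n per arm = 2 × (1.960 + 1.036)² × 24² / 15² = 2 × 8.978 × 2.56 = 45.97, so 46 per arm and 92 in total. This reproduces the stated 92. The noncentral t version gives 47 per arm (94), with power 84.3% at 46 per arm; the gap is immaterial here.

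**4. What a pre-post interval does when rTMS has no effect**

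Set-up: 20,000 simulated trials, 46 per arm, SD of the change score = 1, and the same mean shift g in both arms. The values of g are assumptions; the documents give none for these tests.

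The expected one-sample t value is about g × √46 for one arm and g × √92 for both arms pooled:
- g = 0.2: 1.36 and 1.92
- g = 0.3: 2.03 and 2.88
- g = 0.5: 3.39 and 4.80

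The expected between-arm value is 0 for every g.

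| Common shift g | Active-arm CI excludes 0 | Pooled CI excludes 0 | Active CI excludes 0, sham CI does not | Between-arm test positive |
|---|---|---|---|---|
| 0 | 5.0% | 5.1% | 4.8% | 5.2% |
| 0.2 | 26% | 48% | 20% | 4.9% |
| 0.3 | 51% | 81% | 25% | 5.1% |
| 0.5 | 91% | 99.8% | 8% | 4.8% |

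Reporting the change separately by arm and comparing the two verdicts does not solve the problem: for shifts of 0.2 to 0.3, a positive active arm beside a null sham arm occurs in a fifth to a quarter of trials with no rTMS effect.

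**5. What the between-arm contrast can detect**

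With 46 per arm, an unadjusted t-test has 80% power for a standardised difference of about 0.59 and 85% power for about 0.63. The contrast is usable for moderate to large effects.

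**The case against.** The strongest reply is that the sentence only defines the outcome variable. Section 4 speaks of changes in social cognition, the Background supplies the active-versus-sham comparison, and section 8.1 announces a detailed analysis plan before database lock. In a condensed article the contrast for one secondary outcome can be left to that plan. Part of this stands: the text is silent on the group contrast and does not exclude it. It does not remove the point, because section 8.3 names an estimate for these tests and names a different kind of estimate for the symptom scores beside them.

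A reader might infer more than the documents support:

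- **That a pre-post analysis replaces the comparison, so the trial cannot show any rTMS effect on cognition.** Table 1 schedules the tests before treatment and at visit 15 with no distinction by arm, so the randomised comparison is available. The defect is in the stated estimate.
- **That the V0 label leaves the trial without a baseline.** Visit 1 precedes the first rTMS session. The labels conflict, and the documents do not show which is right.
- **That the size of the non-specific change is known from the earlier cue-exposure trial**, where CAPS went "from 86 (±9.2) to 76 (±10.7) in the EXP-SHAM group", a fall of 86 − 76 = 10 points. That is a symptom scale in nine patients and says nothing about the size of change on these tests.
- **That quality of life also lacks a group contrast.** Section 8.3 says the subscores are to be handled like something earlier in the section. That could mean the between-group difference or the pre-post difference, so the omission is not established.

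It is also fair to say that section 8.3 ties no efficacy claim to the pre-post interval. The percentages above describe what happens if someone uses it as one.

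**Conclusion.** The point holds in limited form. The only analysis stated for social cognition is a pre-post difference. On its own it does not answer the active-versus-sham aim, and it differs in kind from the between-group analyses of the symptom scores in the same section. The baseline visit is given three ways.

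Five tests under one secondary objective are affected. The primary outcome and the sample size are not. The simulated rates of 26% to 91% rest on an assumed shift common to both arms, on 46 evaluable patients per arm, and on reading the active-arm interval as evidence of efficacy. They show the direction and possible scale of the problem and do not forecast this trial's results. The change should be made before the analysis plan is written, so that the pre-post wording is not carried forward. For quality of life, only a clarification is warranted.

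**What to change.** 1. In section 8.3, for each social cognition test, state the between-arm difference at M3 (V15) with 95% CI, adjusted for the pre-treatment value of the same test. At minimum, state the between-arm difference in change with 95% CI, which would match the approach used for the other scores.
2. Keep the within-arm change from baseline to M3 as description only.
3. Reconcile the baseline visit for these tests across section 7.3 (M0), section 8.3 (V0) and Table 1 (visit 1).
4. For WHOQOL and EQ-5D-5L, make explicit that the back-reference in section 8.3 means a between-group difference with 95% CI.

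The cost is wording in the protocol and analysis plan. The tests are already scheduled, so no visit, measurement or change in sample size is needed.
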